### Statistical analysis

#### Sample size

**Step 1 = 268 participants**

The first aim is to show a difference in the proportion of patients with chronic fatigue (≥1 dimension of MFI-20) in the group of interest as compared with each of the control groups. The pairwise comparison will be performed using the χ^2^ test (one-tailed test under the assumption of higher chronic fatigue in the chemotherapy group of interest) at a risk α = 0.05 and a power level of 80% (1-β = 80%). Assuming that 25% of patients express chronic fatigue in the group of interest as described in testicular cancer [20] and 10% in each of the control group, the required sample size, with a 2:1 allocation ratio in favor of the group of interest, is 121 subjects in the group of interest and 61 subjects in each of the two control groups (patient control and healthy control).. To anticipate 10% of non-assessable women, we plan to enroll 134 survivors in the group of interest, 67 survivors in the control group, and 67 healthy controls.

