#### Planned analysis

Data analyses will be conducted according to the statistical methods used in paired case-control studies, as follows:
Descriptive analysis of patients’ and controls’ participation and according to sociodemographic and clinical data (including tumor type), quantitative QoL scores and data on living conditions in patients and controls, and then in patients based on medical data related to cancer.Statistical comparison using a univariate and multivariate analysis (ANOVA, or Kruskal-Wallis test, or Mc Nemar χ2 test depending on the nature of the variables and GLM (Generalized Linear Model) model with a Bonferroni correction):Socio-demographic features and comorbidities;Reintegration and sequelae data, then by subgroup (including fertility-sparing);

A prognostic model for predicting QoL or living conditions has been constructed using an adapted model (GLM), taking into account the time since end of treatment and controlling for effect of center.

Medical and biological parameters are the categorical variables. They will be compared between the two groups of patients and then between sub-groups according to time since end of treatment (short term and long-term follow-up) using the χ2 test or the Fisher exact test.

Costs will be compared using the Wilcoxon-Mann-Whitney test. Standard multivariate analyses will be implemented in order to control the potential selection bias. Uncertainties regarding costs of the sequelae will be assessed by probabilistic analysis using nonparametric bootstrap methods: 1000 simulated bootstrap samples will be generated by independent draws. All 95% confidence intervals will be computed. All analyses will be performed using STATA software version 16.0 (StataCorp, College Station, TX).

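### Step 1: the stated 80% is the power of one uncorrected comparison; the power to show a fatigue difference against each of the two control groups is about 69%, and no decision rule is fixed

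*Protocol article*

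**What the plan says.** The primary objective of Step 1 compares survivors treated with surgery and chemotherapy with two groups, patients treated by surgery alone and age-matched healthy women. Neither is ranked above the other. The sample size section (Step 1 = 268 participants) repeats this: a difference in the proportion with chronic fatigue is to be shown "in the group of interest as compared with each of the control groups".

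The test is a pairwise chi-square, described as a "one-tailed test under the assumption of higher chronic fatigue in the chemotherapy group of interest", and it is set "at a risk α = 0.05 and a power level of 80" per cent. The assumptions are given in full: "Assuming that 25% of patients express chronic fatigue in the group of interest" and "10% in each of the control group", "with a 2:1 allocation ratio in favor of the group of interest". From these the section derives 121 assessable women in the group of interest and 61 in each control group, enrolled as 134/67/67 to allow for 10% non-assessable. It does not divide alpha between the two comparisons, does not give the power to show both differences, and does not say whether one or both must be significant.

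The Planned analysis section names a "GLM (Generalized Linear Model) model with a Bonferroni correction" in a list that also holds ANOVA, Kruskal-Wallis and McNemar tests. The data listed under it are sociodemographic features, comorbidities, reintegration and sequelae. The two one-tailed fatigue tests are not named there.

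**The concern.** An aim that needs a difference against each of two groups is met only if two tests succeed. A calculation that gives 80% for one test gives less for two. If, on the other hand, one success out of two is enough, two full-alpha tests give more than a 5% chance of a false claim. The article states one alpha, one power and one set of numbers, and leaves open which situation applies.

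The stake is the primary question of Step 1. A reader will take 80% as the power for the stated aim, whereas the chance of missing that aim under the plan's own assumptions is about 31%, not 20%. With no rule written down, the choice between requiring both, accepting either, or correcting alpha could be made after the results are seen.

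**Working it through.** **Inputs** (all from the Step 1 sample size paragraph): p1 = 0.25 in the group of interest, p0 = 0.10 in each control group, ratio 2:1, one-sided alpha 0.05, power 80%, assessable numbers 121/61/61, enrolled numbers 134/67/67.

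**1. Reproduce the plan's figure.** Pooled-variance normal formula without continuity correction, for one control group:

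n0 = [z(0.95)·√(p̄(1−p̄)(1+1/2)) + z(0.80)·√(p0(1−p0) + p1(1−p1)/2)]² / (p1−p0)²

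with p̄ = (2×0.25 + 0.10)/3 = 0.20. Then n0 = [1.645×√0.24 + 0.8416×√0.18375]² / 0.0225 = 60.5. This gives 61 controls and 2×60.5 = 121 in the group of interest, an exact match. Adding a continuity correction (141/71) or testing two-sided (156/78) does not match. The plan's numbers are therefore those of one uncorrected one-sided comparison.

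**2. Power of one comparison at 121/61.** Pooled rate (30.25 + 6.1)/182 = 0.1997. Standard error under the null √(0.1997×0.8003×(1/121+1/61)) = 0.0628. Standard error under the alternative √(0.1875/121 + 0.09/61) = 0.0550. Power = Φ[(0.15 − 1.645×0.0628)/0.0550] = Φ(0.85) = 80.2%.

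**3. Power to show both differences at one-sided 0.05.** The two test statistics share the group of interest, so they are correlated: ρ = (0.1875/121)/(0.1875/121 + 0.09/61) = 0.51. The bivariate normal probability that both succeed is 69.2%. Exact binomial enumeration of the same chi-square rule gives 69.6%. (Independent tests would give 0.802² = 64.4%; the shared group raises this.) If all 134/67/67 were assessable, the power for both would be 74.1%. About 152/76/76 assessable women would be needed for 80%.

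**4. Familywise error if either uncorrected test may support a claim.** With 10% fatigue in all three groups, exact enumeration at 121/61/61 gives 4.39% for each test and 0.60% for both, so at least one false positive occurs with probability 2×4.39 − 0.60 = 8.2%.

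**5. If a Bonferroni correction covered these two tests** (one-sided 0.025 each): power per comparison = Φ[(0.15 − 1.960×0.0628)/0.0550] = Φ(0.49) = 68.8% (exact 69.8%). The chance of at least one significant result is 83.2% by the bivariate normal and 86.1% by exact enumeration. Keeping 80% per comparison would need 156/78/78 assessable women.

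| Rule at 121/61/61 | Result |
|---|---|
| One comparison, 0.05 | 80.2% power |
| Both comparisons, each at 0.05 | about 69% power |
| Either comparison, uncorrected | about 8% familywise error |
| One given comparison at 0.025 | about 69% power |
| At least one of two at 0.025 | 83 to 86% power |

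**The case against.** The strongest reply is that alpha and power are stated for the pairwise comparison, and 121/61 delivers exactly that. No stated figure is miscalculated. The two controls also answer different questions, one about chemotherapy and one about the contrast with women without cancer, so a separate alpha for each is defensible in an observational questionnaire study. A full analysis plan, not shown, could settle the order of testing. Most of this stands, and it limits the point to a mismatch between the stated aim and what was sized. It does not remove the mismatch: an analysis plan can choose a rule, but it cannot make 121/61/61 give 80% for both differences.

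Three stronger readings are tempting, and the article does not support them.

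- A reader might infer that the design falls short of 80% under any rule. It does not: if either difference suffices and alpha is split, the chance of at least one success is 83 to 86%. The wording of the aim says each, not either, so this does not rescue the aim as written.
- A reader might take the Bonferroni correction as already planned for the primary tests. The Planned analysis section places it beside the GLM and lists other data. Its reach to the one-tailed fatigue tests is not stated, so the 69% per comparison in step 5 is conditional.
- A reader might add the harms together, or combine an alpha split with a requirement that both tests succeed. If both must succeed, no split is needed and there is no familywise inflation. The 8% error and the 69% joint power are alternatives.

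**Conclusion.** The point holds as a mismatch that should be corrected, not as an arithmetic error. The stated 80% is right for one uncorrected comparison and does not cover the aim of showing a difference against each control group, for which the power is about 69% (about 74% with every enrolled woman assessable). This rests on the plan's own 25% and 10% rates and on the one-tailed chi-square test without continuity correction, and it does not depend on how the Bonferroni sentence is read. The familywise error of about 8% applies only if either uncorrected test may support a claim, and it assumes 10% fatigue in all groups.

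**What to change.** Keep the sample size. In the sample size section, state that 80% is the power per pairwise comparison and that the power to show both differences is about 69%.

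Fix one decision rule before analysis; the article gives the trial's status as still recruiting, so this remains possible. One suitable rule is a fixed sequence: test chemotherapy against surgery alone first at one-sided 0.05, since this is the chemotherapy question; test chemotherapy against healthy women at the same alpha only if the first is significant. This holds familywise error at the nominal 5%, keeps 80% for the first test and gives about 69% for both. Add a sentence saying that the Bonferroni correction in the Planned analysis section does not apply to these two tests.

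The cost is wording, with no extra patients. There are two real downsides: the power stated for the full aim becomes less favourable, and the comparison with healthy women can be tested formally only if the first test succeeds.

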**Step 2 = 135 patients**

Assuming around 66% of patients will accept to participate, 90 patients in the group of interest and 45 patients in patient control group are expected to agree to participate.

Assuming 10% of non-assessable participants (around 80 and 40 survivors in the group of interest and control group, respectively), and a proportion of patients experiencing cardiac sequelae varying from 5 to 35% (with a 95% interval confidence) according to literature for testicular cancer [38], it will be possible to estimate the frequency of cardiac sequelae with a precision of 4.8 to 10.5%, in the group of interest and 6.8 to 14.8% in the control group.

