While follow-up in GCT and SCST ovarian survivors over several years focuses on the risk of recurrence, there is no consensus on follow-up modalities in patients who relapse. Furthermore, the late effects of chemotherapy (metabolic, cardiac, respiratory, renal, hematological disorders, ototoxicity and neurotoxicity) are not routinely investigated. However, follow-up of testicular cancer survivors treated with the same chemotherapy found persistent long-term side-effects of the chemotherapy such as chronic fatigue, cardiovascular and pulmonary disease, neurotoxicity, hypogonadism and a higher risk of secondary cancer. Cisplatin and bleomycin induce alterations in endothelial function and endothelial damage that may trigger vascular diseases [5]. After platinum-based chemotherapy, testicular cancer survivors have a 2-to-3-fold greater risk of cardiovascular disease compared with patients treated with surgery alone or individuals in the general population [6–9]. Raynaud’s syndrome is also a frequent occurrence, with a 2-to-4-fold increased risk after receiving a high platinum dose [10]. In addition, these patients often present a metabolic syndrome, which is a strong predictor of cardiovascular diseases. Metabolic syndrome occurs in 20–30% of long-term testicular cancer patients, and onset is much earlier (3–5 years after treatment) than would be expected in the general population [11, 12]. Other toxicities such as pulmonary toxicity, renal toxicity, ototoxicity and neurological sequelae are frequent and dose-related [13]. According to the available data, the relative risk of a second cancer is approximately doubled after chemotherapy. The estimated cumulative risk of leukemia among testicular cancer survivors who are given etoposide at total doses of less than or equal to 2000 or more than 2000 mg/m2 is 0.5 and 2%, respectively [14].

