#### Step 2:

##### Primary objective

The main objective is to assess the late clinical effects of chemotherapy with a focus on cardiovascular and pulmonary disorders.

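### The Step 2 precision figures are symmetric Wald half-widths, which are too favourable at the 5% end of the planning range, and none is given for the planned between-group comparison

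*Protocol article*

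**What the plan says.** The Step 2 paragraph under Sample size starts from expected uptake: "90 patients in the group of interest and 45 patients in patient control group are expected to agree to participate". After a 10% loss to non-assessable cases it works with "around 80 and 40 survivors in the group of interest and control group, respectively". The planning range is "a proportion of patients experiencing cardiac sequelae varying from 5 to 35% (with a 95% interval confidence"), taken from testicular cancer literature. From these inputs it concludes that "it will be possible to estimate the frequency of cardiac sequelae with a precision of 4.8 to 10.5%, in the group of interest". For the surgery-alone patients the corresponding statement is "6.8 to 14.8% in the control group". No interval method is named.

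The Step 2 primary objective reads: "The main objective is to assess the late clinical effects of chemotherapy with a focus on cardiovascular and pulmonary disorders". Under Planned analysis, the medical and biological parameters are to be compared between the two patient groups by a χ² or Fisher exact test, then again by time since the end of treatment. The Step 2 size paragraph gives no precision, target difference, significance level or power for that comparison.

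**The concern.** The bottom of the planning range, 5%, corresponds to 4 events in 80 and 2 events in 40. With so few events the sampling distribution is clearly skewed, and a symmetric interval around the estimate describes it poorly. It reaches too far down and not far enough up. The upper limit is the one that matters when the question is how frequent a late toxicity could be, so a reader who takes 5% ± 6.8% at face value will believe that control frequencies above about 12% are ruled out when they are not.

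There is a second, related gap. Frequencies within each group cannot by themselves show how much of the sequelae is due to chemotherapy; that rests on the contrast with surgery alone, which the plan intends to test. The uncertainty of that difference is larger than either per-group figure, and the reader is not told how large.

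**Working it through.** **Inputs (Protocol article, Sample size, Step 2).** 90 and 45 enrolled; 10% non-assessable gives 90 × 0.9 = 81 and 45 × 0.9 = 40.5, rounded by the article to about 80 and 40. Assumed frequency 5% to 35%. Confidence 95%.

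**Step 1: reproduce the stated figures.** Wald half-width = 1.96 × √(p(1−p)/n).

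- n = 80, p = 0.05: 1.96 × √(0.0475/80) = 4.78 points (stated 4.8)
- n = 80, p = 0.35: 1.96 × √(0.2275/80) = 10.45 points (stated 10.5)
- n = 40, p = 0.05: 1.96 × √(0.0475/40) = 6.75 points (stated 6.8)
- n = 40, p = 0.35: 1.96 × √(0.2275/40) = 14.78 points (stated 14.8)

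All four match, so the method is Wald with n = 80 and 40.

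**Step 2: compare interval methods.**

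| Events | Wald | Wilson | Clopper-Pearson | Half-width: Wald / Wilson / exact |
|---|---|---|---|---|
| 4/80 (5%) | 0.2 to 9.8% | 2.0 to 12.2% | 1.4 to 12.3% | 4.8 / 5.1 / 5.5 |
| 2/40 (5%) | -1.75 to 11.75% | 1.4 to 16.5% | 0.6 to 16.9% | 6.8 / 7.6 / 8.2 |
| 28/80 (35%) | 24.5 to 45.5% | 25.5 to 45.9% | 24.7 to 46.5% | 10.5 / 10.2 / 10.9 |
| 14/40 (35%) | 20.2 to 49.8% | 22.1 to 50.5% | 20.6 to 51.7% | 14.8 / 14.2 / 15.5 |

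At 35% the half-widths agree within about 0.8 points. At 5% the average half-width grows modestly, but the upper arm grows a good deal: 7.2 to 7.3 points instead of 4.8 at n = 80, and 11.5 to 11.9 instead of 6.8 at n = 40. The lower arm shrinks (exact: 5 − 1.4 = 3.6 and 5 − 0.6 = 4.4 points).

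**Step 3: true coverage of the nominal 95% Wald interval at a true frequency of 5%.** Sum the binomial probabilities of all counts whose Wald interval contains 5%.

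- n = 40: the interval misses at 0 events (probability 0.95^40 = 12.9%) or at 7 or more (0.3%), so coverage is 86.8%.
- n = 80: it misses at 0 or 1 event (8.6%) or at 10 or more (0.7%), so coverage is 90.7%.

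For comparison, Wilson covers 95.2% and 93.7%, and Clopper-Pearson 98.6% and 96.5%, for n = 40 and n = 80 respectively.

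**Step 4: the between-group difference, 80 vs 40.** Newcombe's interval combines the Wilson limits (l, u) of each group, with 1 = chemotherapy and 2 = surgery alone: lower = d − √((p1−l1)² + (u2−p2)²), upper = d + √((u1−p1)² + (p2−l2)²).

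- 10% (8/80, Wilson 5.15 to 18.51) vs 5% (2/40, Wilson 1.38 to 16.50): 5 − √(4.85² + 11.50²) = -7.5; 5 + √(8.51² + 3.62²) = +14.3 points.
- 35% (28/80, Wilson 25.45 to 45.92) vs 17.5% (7/40, Wilson 8.75 to 31.95): 17.5 − √(9.55² + 14.45²) = +0.2; 17.5 + √(10.92² + 8.75²) = +31.5 points.

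**Step 5: power of the χ² comparison, assuming a two-sided 5% level (none is stated for Step 2).** Power = Φ[(d − 1.96·se0)/se1], where se0 uses the pooled proportion and se1 the separate ones.

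- 5% to 10%: se0 = 0.0535, se1 = 0.0481, so Φ(−1.14) = 13%.
- 10% to 20%: se0 = 0.0722, se1 = 0.0652, so Φ(−0.64) = 26%.
- 5% to 15%: 34%; 10% to 30%: 71%; 11.7% to 35%: 81%; 17.5% to 35%: 51%; 5% to 35%: 98%.

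**The case against.** The strongest reply is that nothing is miscalculated. All four figures reproduce, the sentence is a planning statement that does not bind the analysis to Wald intervals, and the choice of interval is normally left to the analysis plan. Like for like, the half-width moves only from 4.8 to 5.1–5.5 and from 6.8 to 7.6–8.2 points, at one end of a wide planning range, and no design decision depends on it. Per-group precision is also a legitimate basis for a study whose size is set by expected uptake in a rare tumour and whose Step 2 objective states no hypothesis.

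Most of this stands. A reader might infer an arithmetic error; there is none. A reader might also infer that both groups' intervals fall below zero; only the control interval at 5% does, since the chemotherapy interval starts at 0.2%. What remains is that the article prints these numbers as 95% precision at its own lower bound, and there they do not deliver 95%. That is a stated figure, not a detail left for later.

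A stronger reading is that Step 2 is underpowered for the effect that the study rests on, because the Background reports a "2-to-3-fold greater risk of cardiovascular disease" after platinum-based chemotherapy. The documents do not support that. The figure is background on testicular cancer survivors; Step 2 is not sized on it and claims no power. Nor is power low throughout the range: a 3-fold rise has about 71% power from a control rate of 10% and about 81% from 11.7%. Low power is confined to low control rates and to 2-fold rises.

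**Conclusion.** The point holds in a limited form. The stated precision is correct Wald arithmetic and adequate at 35%, but too favourable at 5%: true coverage is about 87% for controls and 91% for the chemotherapy group, and the upper limits should be about 16.5 to 16.9% and 12.2 to 12.3% rather than 11.8% and 9.8%. This uses only the article's own inputs.

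Separately, the size statement describes each group alone while the analysis compares them. With 80 and 40 patients the expected interval for the difference spans roughly 22 points at 10% vs 5% (14.3 + 7.5) and 31 points at 35% vs 17.5% (31.5 − 0.2). At control rates of 5 to 10% a 2-fold rise would usually not be detected (power 13 to 26%). These illustrations rest on assumed rates in each group and, for power, on an assumed two-sided 5% level. They show what the comparison can deliver; they do not contradict any power claim in the article, because it makes none for Step 2.

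**What to change.** In the Step 2 size paragraph, replace the low-end half-widths with Wilson or Clopper-Pearson limits and show them as asymmetric intervals: at 5%, 2.0 to 12.2% or 1.4 to 12.3% with 80 patients, and 1.4 to 16.5% or 0.6 to 16.9% with 40. Name the method and use the same one for the reported frequencies.

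Add one sentence giving the expected Newcombe 95% interval for the chemotherapy minus surgery-alone difference with 80 vs 40, for example about -7 to +14 points at 10% vs 5% and about 0 to +31 points at 35% vs 17.5%. Note there that a 2-fold rise from a control rate of 5 to 10% would usually go undetected.

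The cost is a few sentences and a less favourable stated precision. No extra patients, visits or tests are needed.

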### Data management

A Web Based Data management system (Ennov Clinical (version 7.5.10, ENNOV / CLINSIGHT, 33155 Cenon, France)) will be used for data collection and query handling. The investigator will ensure that data are recorded on the electronic case report form CRFs as specified in the study protocol and in accordance with the instructions provided. The data will have to be filled in in these eCRF as they are obtained, and the sponsor will take charge of the monitoring.

The investigator ensures the accuracy, completeness, and timeliness of the data recorded and of the provision of answers to data queries according to the Clinical Study Agreement. A copy of the completed CRFs will be archived at the study site.

All data will be handled and stored according to the EU General Data Protection Regulation (GDPR).

#### Planned analysis

Data analyses will be conducted according to the statistical methods used in paired case-control studies, as follows:
Descriptive analysis of patients’ and controls’ participation and according to sociodemographic and clinical data (including tumor type), quantitative QoL scores and data on living conditions in patients and controls, and then in patients based on medical data related to cancer.Statistical comparison using a univariate and multivariate analysis (ANOVA, or Kruskal-Wallis test, or Mc Nemar χ2 test depending on the nature of the variables and GLM (Generalized Linear Model) model with a Bonferroni correction):Socio-demographic features and comorbidities;Reintegration and sequelae data, then by subgroup (including fertility-sparing);

A prognostic model for predicting QoL or living conditions has been constructed using an adapted model (GLM), taking into account the time since end of treatment and controlling for effect of center.

Medical and biological parameters are the categorical variables. They will be compared between the two groups of patients and then between sub-groups according to time since end of treatment (short term and long-term follow-up) using the χ2 test or the Fisher exact test.

Costs will be compared using the Wilcoxon-Mann-Whitney test. Standard multivariate analyses will be implemented in order to control the potential selection bias. Uncertainties regarding costs of the sequelae will be assessed by probabilistic analysis using nonparametric bootstrap methods: 1000 simulated bootstrap samples will be generated by independent draws. All 95% confidence intervals will be computed. All analyses will be performed using STATA software version 16.0 (StataCorp, College Station, TX).

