**Methods:**

Using self-reported questionnaires, chronic fatigue and quality of life are compared between 134 ovarian cancer survivors (cancer-free ≥2 years after treatment) treated with surgery and chemotherapy and 2 control groups (67 ovarian cancer survivors treated with surgery alone and 67 age-matched healthy women). Medical data are collected from patient records. In the second step evaluating the long-term side-effects of chemotherapy, a subgroup of 90 patients treated with chemotherapy and 45 controls undergo the following work-up: cardiovascular evaluation (clinical examination, non-invasive cardiovascular tests to explore heart disease, blood tests), pulmonary function testing, audiogram, metabolic and hormonal blood tests. Costs of sequelae will be also assessed. Patients are selected from the registry of the INCa French Network for Rare Malignant Ovarian Tumors, and healthy women by the ‘Seintinelles’ connected network (collaborative research platform).

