### Study participants

**134 adult ovarian GCT or SCST survivors in remission ≥ 2 years after treatment** with **surgery and BEP chemotherapy** (≥ 1 cycle) (recurrence occurs mainly in first 2 years after initial treatment) are compared to **two groups of controls**:
**Patient control group:** 67 adult ovarian GCT or SCST survivors in remission ≥2 years after treatment with surgery alone;**Healthy control group:** 67 age-matched (±2 years) healthy women without cancer and without serious chronic diseases.

Eligible patients of interest and control groups are recruited from the INCa French network TMRG. These patients have been selected by the oncologists of the French cooperative GINECO group (Groupe d’Investigateurs Nationaux pour l’Étude des Cancers Ovariens et du sein). There are 19 participating centers. Healthy women age-matched with patients of interest are recruited from the Seintinelles® network (https://www.seintinelles.com/home). Seintinelles® is a collaborative research platform linking researchers and citizens to accelerate cancer research. Female cancer-free volunteers will be contacted to complete online self-questionnaires. Inclusion and exclusion criteria are detailed in Table 1. A coordinating committee was set up before the conception of the research including the scientific team of TMRG and GINECO and cardiologists.

**Table 1 Tab1:** Study inclusion and exclusion criteria

	Group of interest	Patient control group	Healthy control group
Step 1	**134** ovarian Germ Cell Tumor or Sex Cord Stromal tumor survivors	**67** ovarian Germ Cell Tumor or Sex Cord Stromal tumor survivors	**67** healthy women
Step 2	**90** ovarian Germ Cell Tumor or Sex Cord Stromal tumors survivors	**45** ovarian Germ Cell Tumor or Sex Cord Stromal tumor survivors	**Not applicable**^**a**^
Inclusion criteria	≥ 18 years old	≥ 18 years old	≥ 18 years old
		Age-matched to group of interest (± 2 years)	Age-matched to group of interest (± 2 years)
	Patient treated with **surgery** and **BEP chemotherapy** (≥ 1 cycle)	Patient treated with **surgery alone** (with or without fertility sparing).	
	Patient in remission ≥2 years after initial treatment	Patient in remission ≥2 years after initial treatment	
	Recurrence authorized if remission more than 2 years after end of initial treatment	Recurrence authorized if remission more than 2 years after the end of initial treatment	

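### Step 1 is sized and stated as an unpaired 2:1 χ² comparison, but the Planned analysis section prescribes paired case-control methods and McNemar, which do not fit that design

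*Protocol article*

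**What the plan says.** **Sample size (Step 1).** Chronic fatigue is a yes/no outcome (at least one MFI-20 dimension). The group of interest is compared with each control group by a χ² test, described as a "one-tailed test under the assumption of higher chronic fatigue in the chemotherapy group of interest", with α = 0.05 and 80% power. The assumed rates are 25% and 10%. The calculation is made "with a 2:1 allocation ratio in favor of the group of interest" and gives 121 evaluable women against 61 in each control group. Enrolment is 134, 67 and 67.

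**Planned analysis.** The governing sentence is "Data analyses will be conducted according to the statistical methods used in paired case-control studies". The group comparisons use ANOVA, Kruskal-Wallis, "or Mc Nemar χ2 test depending on the nature of the variables", together with a multivariate GLM with a Bonferroni correction. The items listed under these tests are socio-demographic features, comorbidities, and reintegration and sequelae data. The medical and biological parameters of Step 2 are compared with χ² or Fisher tests, which are unpaired.

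**Matching.** Table 1 has the entry "Age-matched to group of interest (± 2 years" (closing bracket omitted here) under both control groups. The abstract describes the controls as "67 ovarian cancer survivors treated with surgery alone and 67 age-matched healthy women". The primary objective and the group list under Study participants likewise attach age-matching to the healthy women only. No matching ratio or set structure is given.

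**The concern.** The two sections describe different studies. One has independent groups of unequal size. The other has pairs. A binary variable such as chronic fatigue falls under the paired rule of the Planned analysis section, and that section does not exempt it; the sample-size section sends the same variable to an unpaired test.

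The paired rule also does not fit the design. Ordinary McNemar works on one-to-one pairs, and there are two chemotherapy survivors for every control. The article's own list mixes frameworks, since ANOVA and Kruskal-Wallis are unpaired. The case-control label does not help either: women are grouped by treatment received and compared on fatigue, which is the outcome.

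At stake is which test is run on the primary endpoint. If this stays open, the choice could be made after the data are seen. A crude test of either kind also leaves a gap in the chemotherapy versus surgery-alone contrast. The Background says that chemotherapy depends on stage and prognostic factors in germ cell tumours and is given for extensive or recurrent disease in sex cord stromal tumours. It also gives the two tumour types different age profiles.

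**Working it through.** **Inputs from the article (Sample size, Step 1):** p1 = 0.25, p0 = 0.10, difference d = 0.15, one-sided α = 0.05 (z = 1.645), power 80% (z = 0.842), ratio 2:1, evaluable 121 and 61, enrolled 134 and 67.

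**Input assumed:** within-pair correlation φ of fatigue, from 0 to 0.3. The article gives no value.

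**1. Reproducing the stated size.** For independent groups, pooled variance, no continuity correction, the pooled rate is (2 × 0.25 + 0.10)/3 = 0.20, and the control-group size is

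n0 = [1.645·√(0.20 × 0.80 × 1.5) + 0.842·√(0.25 × 0.75/2 + 0.10 × 0.90)]² / 0.15² = 60.5.

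This gives 61 controls and 2 × 60.5 = 121 in the group of interest, as stated. Other versions do not match:

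| Version | Group of interest / control |
|---|---|
| One-sided, pooled, uncorrected | 121 / 61 |
| One-sided, continuity-corrected | 141 / 71 |
| One-sided, unpooled | 101 / 51 |
| Two-sided, pooled, uncorrected | 156 / 78 |

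So the size assumes no pairing. Power at 121 and 61: the standard error is 0.0628 under the null and 0.0550 under the alternative, so z = (0.15 − 1.645 × 0.0628)/0.0550 = 0.85 and power is 80.2%.

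**2. What one-to-one pairing would leave out.** 121 − 61 = 60 evaluable chemotherapy survivors in each comparison, or 134 − 67 = 67 as enrolled.

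**3. Power if McNemar were applied to fatigue.** With p11 = p1·p0 + φ·√[p1(1 − p1)·p0(1 − p0)], the discordant probabilities are p10 = 0.25 − p11 and p01 = 0.10 − p11, and their sum is pd. By the normal approximation,

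power = Φ{[d·√n − 1.645·√pd] / √(pd − d²)}.

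At φ = 0: p11 = 0.025, p10 = 0.225, p01 = 0.075, pd = 0.30. With n = 61, z = (0.15 × √61 − 1.645 × √0.30)/√(0.30 − 0.0225) = 0.51, so power is 69.6%.

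| φ (assumed) | pd | Power, 61 pairs | Power, 67 pairs | Pairs for 80% |
|---|---|---|---|---|
| 0 | 0.300 | 69.6% | 73.3% | 81 |
| 0.1 | 0.274 | 73.2% | 76.8% | 74 |
| 0.2 | 0.248 | 77.1% | 80.5% | 67 |
| 0.3 | 0.222 | 81.3% | 84.5% | 59 |

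With 61 evaluable pairs the stated 80% is reached only when φ is near 0.3. The 67-pair column supposes that every enrolled woman is assessable, contrary to the article's own 10% allowance.

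**4. Adjustment.** The sentence that names McNemar also plans a multivariate GLM, but does not link it to the fatigue comparison. Time since end of treatment and center are named for the model predicting quality of life or living conditions. Multivariate control of selection bias is named in the cost paragraph.

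**The case against.** The strongest reply is that the primary test is already fixed. The sample-size section names the χ² for chronic fatigue, uses every assessable woman and reproduces its own figures. McNemar is only one option according to variable type, and fatigue is not among the items listed beneath it. This largely stands. A reader might infer that the primary comparison as planned discards half of the chemotherapy group, or that the trial has only 70% power. The article supports neither: both follow only if McNemar is carried over to fatigue on one-to-one pairs, and the 70% also needs a correlation near zero. What remains is that the paired rule is worded to cover the analyses generally and makes no exception for fatigue.

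A reader might also infer that the plan has no adjustment at all. It does plan a multivariate GLM, and the detail of covariates may properly sit in the full protocol or the SAP. The point is therefore the contradiction between the sections, not a missing covariate list.

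On matching, Table 1 is where the article says its criteria are detailed, and the other places omit matching for the surgery-alone group without denying it. That is an unevenness in wording, and the case-control label is likewise minor by itself. Both still bear on whether a matched analysis is appropriate.

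**Conclusion.** The Planned analysis and Sample size sections name incompatible analyses, and the paired one does not fit a 2:1 design without described matched sets. This part rests on the text alone. The sample size is correctly derived for the χ² test that the article states.

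The consequence is conditional. Ordinary McNemar would leave out 60 of 121 evaluable chemotherapy survivors in each comparison. On fatigue its power would be about 70% to 81% over an assumed within-pair correlation of 0 to 0.3, against 80.2% for the independent χ². These figures assume the article's 25% and 10% rates, 61 one-to-one pairs and the normal approximation.

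Because the contradiction touches the primary endpoint and costs little to remove, it should be settled before analysis. An age-adjusted analysis of all women, with further adjustment in the patient contrast, would also serve the question better than a crude χ² or McNemar alone.

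**What to change.** 1. In Planned analysis, delete McNemar and the sentence invoking paired case-control methods.
2. Keep the χ² of the sample-size section as the unadjusted test for fatigue.
3. Specify the planned GLM for fatigue as a logistic regression on group using all women (134 + 67 + 67 = 268 enrolled), adjusted for age. For chemotherapy versus surgery alone (134 + 67 = 201 patients), also adjust for tumour type and time since end of treatment, which have no value in healthy women.
4. Add stage if it is available. The article's list of data taken from patient records does not name it, and confounding by stage would remain without it.
5. If 2:1 matched sets are really formed, state the ratio and use conditional logistic regression on the sets instead of item 3.
6. Make Table 1 agree with the abstract, the primary objective and the Study participants text on whether surgery-alone patients are age-matched.

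The cost is wording in the analysis section and one reconciliation of the eligibility text. Tumour type and time since end of treatment already appear in the planned analyses and age is the matching factor, so no new data are needed unless stage has to be extracted. The sample size does not change.
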